## Abstract

**Background:**

Cancer chemotherapy indications for patients with poor performance status and advanced lung cancer are limited. Molecular targeted drugs, including epidermal growth factor receptor (EGFR)-tyrosine kinase inhibitors, can be used in patients with poor performance status owing to their high efficacy and safety. The third-generation EGFR-tyrosine kinase inhibitor osimertinib has demonstrated effectiveness in the initial treatment of advanced EGFR mutation-positive non-small cell lung cancer in patients with good performance status; however, no evidence exists of the drug’s effectiveness in patients with poor performance status in a prospective study. We designed a study that aims to investigate the efficacy and safety of first-line osimertinib treatment in patients with advanced non-small cell lung cancer harboring sensitive EGFR mutations and with poor performance status.

**Methods:**

The OPEN/TORG2040 study is a multicenter, single-arm, phase II trial for patients with unresectable, advanced EGFR mutation-positive non-small cell lung cancer with a poor performance status (≥ 2). Eligible patients will receive osimertinib until disease progression or unacceptable toxicity. The primary endpoint is the objective response rate of the first-line osimertinib treatment. Considering a threshold value of 45%, expected value of 70% for objective response rate, one-sided significance level of 5%, statistical power of 80%, and ineligible patients, the sample size was set to 30. The secondary endpoints are disease control rate, performance status improvement rate, and safety and patient-reported outcomes using the European Organization for Research and Treatment of Cancer Quality of Life Questionnaire-Core Quality of Life Questionnaire and Lung Cancer 13. Time to treatment failure, progression-free survival, and overall survival will also be assessed.

**Discussion:**

Our study can determine the clinical benefits of osimertinib treatment in patients with poor performance status, since the clinical outcomes of patients with EGFR mutation-positive non-small cell lung cancer with poor performance status treated with this drug as a first-line treatment have not been sufficiently evaluated.

**Trial registration:**

Japan Registry of Clinical Trials: jRCTs041200100 (registration date: February 12, 2021).

## Background

Epidermal growth factor receptor (EGFR) gene mutations have been identified as predictors of the effect of EGFR-tyrosine kinase inhibitors (TKIs) on EGFR mutation-positive non-small cell lung cancer (NSCLC) [1–3]. Among the EGFR gene mutations, exon 19 deletions (DEL) and exon 21 L858R point mutations, which account for approximately 90% of the total mutations, and uncommon mutations, such as exon 18 G719X and exon 21 L861Q, are known to be EGFR-TKI-sensitizing mutations [4, 5]. In addition, a T790M mutation has been identified in approximately half of the patients as a resistance factor to first- and second-generation EGFR-TKIs, such as gefitinib, erlotinib, afatinib and dacomitinib.

Osimertinib is a third-generation, irreversible EGFR-TKI that selectively inhibits both EGFR-TKI-sensitizing and EGFR-T790M-resistant mutations [6, 7]. In a double-blind, phase III trial (FLAURA), osimertinib showed efficacy superior to that of first-generation gefitinib or erlotinib in the first-line treatment of EGFR mutation (DEL or L858R)-positive advanced NSCLC, with a similar safety profile and lower rates of serious adverse events [8, 9]. Osimertinib is currently being used as the first-line treatment for patients with advanced EGFR mutation-positive NSCLC in clinical practice. However, in the FLAURA trial, patients with a performance status (PS) of 0 to 1 were eligible, and the efficacy and safety of osimertinib treatment in patients with EGFR mutation-positive NSCLC with a poor PS (2 or more) have not been fully verified.

Poor PS is a known adverse prognostic factor in advanced NSCLC [10, 11] and a risk factor for serious adverse events, including drug-induced interstitial lung disease [12]. The median survival of patients with advanced NSCLC who are not eligible for cytotoxic chemotherapy due to poor PS was reported about 3–4 months [13, 14]. A previous prospective study of first-line gefitinib treatment for patients with advanced EGFR mutation (DEL, L858R, G719X or L861Q)-positive NSCLC without indication for cytotoxic chemotherapy as a result of poor PS has supported the use of EGFR-TKIs for these patients [15]. Several studies have indicated that osimertinib could be beneficial in patients with poor PS and EGFR T790M mutation-positive NSCLC following the progression of first- and second-generation EGFR-TKI treatments [16–19]. However, the existing data are insufficient to determine the efficacy and safety of osimertinib in chemo-naïve patients with EGFR mutation-positive NSCLC and poor PS.

First-line osimertinib treatment for patients with poor PS could be beneficial and clinically meaningful, considering the limited benefits of cytotoxic chemotherapy. Thus, this study aims to assess the efficacy and safety of first-line osimertinib treatment in patients with poor PS and advanced NSCLC harboring sensitizing EGFR mutations.

## Design

### Study design and treatment

This study, whose objective is to assess the efficacy and safety of first-line osimertinib treatment in patients with advanced NSCLC harboring sensitive EGFR mutations and with poor PS, was designed as a multicenter, single-arm, phase II trial conducted by the Thoracic Oncology Research Group (TORG) in accordance with the Declaration of Helsinki. The study schema is illustrated in Fig. 1. The protocol was approved by the National Hospital Organization Nagoya Medical Center Certified Review Board of Clinical Research (approval date: December 21, 2020; approval number: C2020-010). This clinical trial was registered in the Japan Registry of Clinical Trials (registration date: February 12, 2021; registry number: jRCTs041200100). Registration for this study begin in February 2021 and will end in August 2022. Eligible patients with EGFR mutation-positive NSCLC and with a PS of 2 to 4 will receive osimertinib (80 mg orally, once daily) until disease progression or unacceptable toxicity. However, if the patients continue to show clinical benefit with the treatment as judged by the investigator, they may continue to receive osimertinib beyond the progression defined by the Response Evaluation Criteria in Solid Tumors (RECIST) version 1.1.

**Fig. 1 Fig1:**
[figure not shown]
OPEN/TORG2040 study design. *NSCLC* non-small cell lung cancer, *ECOG* Eastern Cooperative Oncology Group, *PS* performance status, *EGFR* epidermal growth factor receptor, *DEL* deletion, *QTc* corrected QT

### Eligibility criteria

Each patient’s general condition will be assessed using the Eastern Cooperative Oncology Group PS, and patients with PS ≥ 2 will be eligible for this study. The key patient inclusion and exclusion criteria are listed in Table 1. After their eligibility is confirmed, the patients will be asked to provide informed consent. Patient registration began in February 2021 and should continue for 1.5 years.

**Table 1 Tab1:** Key eligibility criteria

Inclusion criteria	
1	Histologically or cytologically proven NSCLC
2	NSCLC with sensitizing EGFR mutations (exon 18 G719X, exon 19 deletions, exon 21 L858R, and exon 21 L861Q)
3	Unresectable NSCLC with stage III/IV cancer or postoperative recurrence
4	Age 20 years or older
5	ECOG PS 2–4 owing to NSCLC and life expectancy of more than 12 weeks
6	At least one measurable lesion according to RECIST version 1.1
7	No prior cytotoxic chemotherapy, immune-checkpoint inhibitor, or targeted agent, including EGFR-tyrosine kinase inhibitor
8	Adequate laboratory data within 14 days before registration
	a) Neutrophil count ≥1500/mm^3^
	b) Hemoglobin ≥9.0 g/dL
	c) Platelet count ≥100,000/mm^3^
	d) Aspartate aminotransferase ≤2.5 times the normal value upper limit
	e) Alanine aminotransferase ≤2.5 times the normal value upper limit
	f) Total bilirubin ≤1.5 times the normal value upper limit
	g) Creatinine ≤1.5 times the normal value upper limit or creatinine clearance < 50 mL/min (Cockcroft–Gault formula)
	h) SpO_2_ ≥ 90% (with or without oxygen therapy)
9	Written informed consent

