### Statistical analysis

A previous Japanese study for patients with EGFR mutation-positive NSCLC without indication for cytotoxic chemotherapy as a result of poor PS, which included 26 of 30 patients with PS 2 to 4, reported that first-line gefitinib had an ORR of 66% (90% confidence interval [CI], 51 to 80%) [15]. Retrospective studies of first-line or second-line EGFR-TKI treatment for patients with EGFR mutation-positive NSCLC with PS 2 to 4 showed an ORR of 16.4 to 70.0% [13, 16, 17, 20]. Although there was insufficient evidence for first-line osimertinib in EGFR mutation-positive patients with poor PS, our prospective observational study reported an ORR of 56.3% (95% CI: 47.1 to 78.0%) [21]. This study is to confirm similar efficacy of gefitinib monotherapy and safety; therefore, the threshold of ORR was set to 45%. In the Japanese PS 0 to 1 population of the FLAURA trial, the ORRs of osimertinib and gefitinib were 75.4 and 76.4%, respectively [9]. Since the patients in this study should have PS 2 to 4, the expected ORR was set to 70%. With a threshold value of 45% and expected value of 70% for ORR, one-sided significance level of 5%, and statistical power of 80%, and by taking ineligible patients into account, the sample size was set to 30 patients.

The patients who meet the key eligible criteria and receive at least one trial treatment will comprise the full-analysis set (FAS). Within the FAS, an analysis set that does not have a serious protocol violation is defined as the per-protocol set. FAS will be used for the primary efficacy analysis. All patients who receive at least one trial treatment will be analyzed for safety.

The exact 90% CI of ORR will be estimated using the Clopper–Pearson method. A binomial test with a one-sided significance level of 0.05 will be performed based on the null hypothesis that the ORR is below the 45% threshold. The 95% CI for disease control rate and proportion of PS improvement will be estimated. The percent of change from baseline for EORTC QLQ-C30 and LC13 will be calculated. The worst grade of adverse event will be summarized. The survival curves for time to treatment failure, progression-free survival, and overall survival will be estimated using the Kaplan–Meier method.

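### Inclusion criterion 8g contradicts its own heading: once creatinine exceeds 1.5 times the upper limit, it admits clearance below 50 mL/min and refuses clearance of 50 or more

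*Protocol article*

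**What the plan says.** The Eligibility criteria section of the Protocol article points to its table: "The key patient inclusion and exclusion criteria are listed in Table 1". Inclusion criterion 8 in that table is headed "Adequate laboratory data within 14 days before registration" and has eight lines, 8a to 8h. Line 8g reads "Creatinine ≤1.5 times the normal value upper limit or creatinine clearance < 50 mL/min", with clearance taken from the Cockcroft–Gault formula.

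The Statistical analysis section then makes eligibility part of the definition of the primary population: "The patients who meet the key eligible criteria and receive at least one trial treatment will comprise the full-analysis set (FAS"). It adds "FAS will be used for the primary efficacy analysis". Safety is handled separately: "All patients who receive at least one trial treatment will be analyzed for safety".

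**The concern.** The heading says that the lines below it define adequate laboratory values. Seven of the eight lines do so by limiting the value on its unfavourable side. Line 8g starts in the same way with creatinine, but then offers, as an alternative way to qualify, a creatinine clearance below a cut-off. Lower clearance means worse renal function, so this branch runs against the heading.

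Two things are at stake. The line is one of the screening criteria, and as printed it sorts patients with raised creatinine in the opposite direction from what its heading announces. It also helps to decide who counts as eligible for the FAS, and hence who is in the denominator of the primary objective response rate (ORR). If the printed line and the line used for screening differ, the same treated patient can be inside the FAS under one and outside it under the other.

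**Working it through.** **1. The sibling lines.** Neutrophils, hemoglobin, platelets and SpO2 (8a, 8b, 8c, 8h) carry a minimum, for example "Platelet count ≥100,000/mm^3". Aspartate aminotransferase, alanine aminotransferase and bilirubin (8d, 8e, 8f) carry a maximum. All seven limit the value on its unfavourable side, as does the creatinine branch of 8g. The clearance branch is the only exception. The other inequality signs in the same table read correctly, so a fault in extracting the text is an unlikely explanation.

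**2. The logic of 8g.** The rule as printed is: pass if (creatinine ≤ 1.5 × ULN) or (clearance < 50 mL/min).

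| Creatinine | Clearance | 8g as printed |
|---|---|---|
| ≤ 1.5 × ULN | ≥ 50 | pass (first branch) |
| ≤ 1.5 × ULN | < 50 | pass (both branches) |
| > 1.5 × ULN | < 50 | pass (second branch) |
| > 1.5 × ULN | ≥ 50 | fail |

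The only patients refused are those in the last row. Among patients with raised creatinine, they are the ones with the better clearance.

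**3. Worked pairs.** The last column reverses the sign of the clearance branch. It is there only to show which patients depend on the sign; it is not a proposed criterion.

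| Creatinine (× ULN) | Clearance (mL/min) | As printed | Sign reversed |
|---|---|---|---|
| 1.0 | 80 | pass | pass |
| 1.0 | 40 | pass | pass |
| 2.0 | 60 | fail | pass |
| 2.0 | 45 | pass | fail |
| 3.0 | 25 | pass | fail |
| 6.0 | 10 | pass | fail |

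The sign matters only when creatinine exceeds 1.5 × ULN. For every such patient it reverses the answer.

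**4. Other renal limits.** Table 1 has none. Exclusion 8 (serious uncontrolled illness) and exclusion 15 (a general unsuitability clause) could remove some of these patients, but at the investigator's discretion and without a renal value.

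**5. Link to the analysis sets.** The FAS requires the key criteria plus at least one dose, and Table 1 is where the key criteria are listed. Line 8g is therefore part of the FAS definition. The safety set requires only treatment, so it does not depend on 8g.

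**6. Sample size.** Inputs from the Statistical analysis section: null ORR p0 = 0.45, expected ORR p1 = 0.70, one-sided alpha 0.05, power 80%, n = 30 including an unstated allowance for ineligible patients. For each n, take the smallest r with P(X ≥ r | n, 0.45) ≤ 0.05; power is P(X ≥ r | n, 0.70).

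| n | r | Exact alpha | Power |
|---|---|---|---|
| 24 | 16 | 0.027 | 0.725 |
| 25 | 16 | 0.044 | 0.811 |
| 26 | 17 | 0.029 | 0.770 |
| 27 | 17 | 0.046 | 0.843 |
| 28 | 18 | 0.031 | 0.809 |
| 29 | 18 | 0.049 | 0.871 |
| 30 | 19 | 0.033 | 0.841 |

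The first n that reaches 80% power is 25. The normal approximation gives 24, or 28 with a continuity correction. A requirement of 25 to 28 leaves 30 − 28 = 2 to 30 − 25 = 5 places for ineligible patients, so the plan's figure of 30 is reproduced. None of these inputs involves 8g. The rows below 30 only illustrate what a smaller FAS would do. Power does not fall steadily, because r moves in whole steps, and nothing in the document says how many patients, if any, would be lost.

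**The case against.** The strongest reply is that this is a table of key criteria in a journal article. The Study design section refers to a protocol approved in December 2020, which is not shown. The fault may be a misprint in the article, with sites screening from a correct line. That stands. It limits what can be said about harm, but it does not rescue the printed line, which is a wrong statement and not a detail left to a fuller document.

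A reader might infer that the trial admits patients with poor renal function without limit. The documents support that only for line 8g read alone. Exclusions 8 and 15 still allow removal, although they do not cure the line. A reader might also infer that sites are enrolling the wrong patients. Nothing shows that they screen from this table.

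It might further be thought that changing the one symbol would put a limit on clearance for everyone. It would not: the two branches are joined by an or, so anyone with creatinine at or below 1.5 × ULN passes at any clearance.

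Finally, the group that the printed line refuses may be small. As an illustration with assumed patients, Cockcroft–Gault clearance for a man is (140 − age) × weight / (72 × creatinine). At age 70 and 60 kg, clearance of at least 50 needs creatinine no higher than 70 × 60 / (72 × 50) = 1.17 mg/dL. For that also to exceed 1.5 × ULN, the ULN must lie below 1.17 / 1.5 = 0.78 mg/dL. At age 50 and 80 kg the limits are 90 × 80 / 3600 = 2.0 mg/dL and a ULN below 1.33 mg/dL. The article gives no ULN, so the size of the group stays open. This argument does not touch the patients whom the line admits at low clearance.

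**Conclusion.** The point holds as an internal contradiction. Under a heading about adequate values, the clearance branch of 8g admits the worse value and refuses the better one whenever creatinine exceeds 1.5 × ULN, and the line sets no lower bound on clearance. It is an operative rule, because the FAS, which carries the primary ORR analysis, is defined by the key eligibility criteria.

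Its size is limited. Patients with creatinine at or below 1.5 × ULN are unaffected, the number of other patients cannot be derived, and sample size, alpha and the safety set do not depend on the line. A claim that the trial's power is damaged would go beyond the document. The conclusion rests on two assumptions: that the or is meant literally, and that the key criteria in the FAS definition are those in Table 1, as the Eligibility criteria section indicates. Whether the fault goes further than the article depends on the approved protocol, which only the sponsor can check.

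**What to change.** First, compare 8g with the approved protocol. Then reconcile the line with its heading, with the sponsor's clinicians confirming both the direction and the value of the clearance branch; no value or direction is proposed here. Correct the article, and state, before the FAS is fixed, which version of 8g governs FAS membership. The cost is the comparison of one line, an erratum and one sentence in the analysis documents.

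If the approved protocol carries the same line, also notify the sites and re-check the patients already registered. With a planned 30 patients, that is a short review of screening creatinine and clearance, needed only where creatinine exceeded 1.5 × ULN. If the approved protocol is free of the contradiction, the erratum and the statement on the FAS close the matter.

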**Exclusion criteria**	
1	EGFR exon 20 insertions
2	Synchronous or metachronous active double malignancies
3	History of interstitial lung disease, drug-induced pneumonitis, radiation pneumonitis requiring systemic steroid therapy, or active interstitial pneumonitis
4	Ingestion not possible or refractory nausea and vomiting
5	Presence of active infections requiring antibiotics
6	Severe psychological disorder
7	Active brain metastasis
8	Serious uncontrolled medical conditions
9	Systemic administration of steroids for 4 weeks or longer (prednisolone-equivalent doses within 20 mg/day are allowed)
10	ECOG PS reduction due to comorbidities
11	Major surgery or radiation therapy with more than 30% of bone marrow or widespread radiation within 4 weeks prior to enrollment
12	QT prolongation on resting electrocardiogram (QTc ≥ 470 ms)
13	History of hypersensitivity to osimertinib
14	Pregnant, currently breastfeeding, positive pregnancy test results, or unwilling to practice contraception during this study
15	Other conditions not suitable for this study

*NSCLC* non-small cell lung cancer, *EGFR* epidermal growth factor receptor, *ECOG* Eastern Cooperative Oncology Group, *PS* performance status, *RECIST* Response Evaluation Criteria in Solid Tumors, *QTc* corrected QT

### Evaluation of treatment efficacy

Computed tomography scans of the chest and abdomen, a computed tomography or magnetic resonance imaging scan of the brain, a bone scan or positron emission tomography scan, blood test, urine test, electrocardiography, and echocardiography are required before initiation of study treatment. Patients will undergo a tumor assessment, Eastern Cooperative Oncology Group PS evaluation, and patient-reported outcome assessments using the European Organization for Research and Treatment of Cancer (EORTC) Quality of Life Questionnaire (QLQ)-Core Quality of Life Questionnaire (C30) and Lung Cancer 13 (LC13) at baseline, every 6 weeks (± 2) during the first 24 weeks, and every 8 weeks (± 2) thereafter. The tumor response will be evaluated in accordance with RECIST version 1.1. Adverse events will be recorded using the National Cancer Institute’s Common Terminology Criteria for Adverse Events version 5.0.

### Endpoints

The primary endpoint is the objective response rate (ORR) of first-line osimertinib treatment. ORR is defined as the proportion of patients whose best response is complete response or partial response. However, response evaluation following the initiation of other anticancer treatments is not employed.

The secondary endpoints are disease control rate, proportion of PS improvement, safety, and patient-reported outcomes. In addition, the time to treatment failure, progression-free survival, and overall survival will also be assessed. Disease control rate is the proportion of patients whose best response is complete response, partial response, or stable disease. Proportion of PS improvement is defined as the proportion of patients who have improved by one or more steps from baseline after the start of study treatment. The time to treatment failure is defined as the duration from registration to the first date of disease progression, death, or stop of the trial treatment. Progression without diagnostic imaging is also included in disease progression. Survivors who have not progressed and continue treatment on their last visit will be censored at the last date of observation. Progression-free survival is defined as duration from registration to the confirmation of disease progression or the date of death. A survivor without disease progression is censored at the date of evaluation based on RECIST. Overall survival is the duration from registration to all causes of death. A survivor is censored at the last date of observation.

### Statistical analysis

A previous Japanese study for patients with EGFR mutation-positive NSCLC without indication for cytotoxic chemotherapy as a result of poor PS, which included 26 of 30 patients with PS 2 to 4, reported that first-line gefitinib had an ORR of 66% (90% confidence interval [CI], 51 to 80%) [15]. Retrospective studies of first-line or second-line EGFR-TKI treatment for patients with EGFR mutation-positive NSCLC with PS 2 to 4 showed an ORR of 16.4 to 70.0% [13, 16, 17, 20]. Although there was insufficient evidence for first-line osimertinib in EGFR mutation-positive patients with poor PS, our prospective observational study reported an ORR of 56.3% (95% CI: 47.1 to 78.0%) [21]. This study is to confirm similar efficacy of gefitinib monotherapy and safety; therefore, the threshold of ORR was set to 45%. In the Japanese PS 0 to 1 population of the FLAURA trial, the ORRs of osimertinib and gefitinib were 75.4 and 76.4%, respectively [9]. Since the patients in this study should have PS 2 to 4, the expected ORR was set to 70%. With a threshold value of 45% and expected value of 70% for ORR, one-sided significance level of 5%, and statistical power of 80%, and by taking ineligible patients into account, the sample size was set to 30 patients.

The patients who meet the key eligible criteria and receive at least one trial treatment will comprise the full-analysis set (FAS). Within the FAS, an analysis set that does not have a serious protocol violation is defined as the per-protocol set. FAS will be used for the primary efficacy analysis. All patients who receive at least one trial treatment will be analyzed for safety.

The exact 90% CI of ORR will be estimated using the Clopper–Pearson method. A binomial test with a one-sided significance level of 0.05 will be performed based on the null hypothesis that the ORR is below the 45% threshold. The 95% CI for disease control rate and proportion of PS improvement will be estimated. The percent of change from baseline for EORTC QLQ-C30 and LC13 will be calculated. The worst grade of adverse event will be summarized. The survival curves for time to treatment failure, progression-free survival, and overall survival will be estimated using the Kaplan–Meier method.

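### Percent change from baseline is a poor summary for the EORTC scores: undefined at a zero baseline, and dependent on the starting score elsewhere

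*Protocol article*

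**What the plan says.** The Endpoints section of the protocol article makes patient-reported outcomes a secondary endpoint: "The secondary endpoints are disease control rate, proportion of PS improvement, safety, and patient-reported outcomes". The Evaluation of treatment efficacy section names the EORTC QLQ-C30 and LC13 as the instruments and schedules them "at baseline, every 6 weeks (± 2) during the first 24 weeks, and every 8 weeks (± 2) thereafter". The Statistical analysis section then gives the only analysis stated for them: "The percent of change from baseline for EORTC QLQ-C30 and LC13 will be calculated".

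The article does not give the scoring range of the two questionnaires. It does not mention absolute change in points, and it has no rule for a baseline score of zero. The planned size is 30 patients.

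**The concern.** Percent change divides by the baseline score. On a scale where 0 is a possible score, the division fails for patients who start there, and for low starting scores a small move becomes a very large percentage. The choice of metric is written into the plan, so this is not a detail left open for a later document.

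The patients without a value would not be a random subset. Under the usual scoring direction (also an assumption), a patient at 0 on a symptom scale has no symptom and can only stay the same or worsen. A patient at 0 on a functional scale is at the floor and can only stay the same or improve. The trial enrols patients with performance status 2 to 4, and its Discussion stresses recovery from poor physical condition, so these scores matter to its message. With a single arm, no control group shares the distortion, and it passes straight into the reported result.

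**Working it through.** **Inputs from the article.** The metric is percent change from baseline for both questionnaires (Statistical analysis). The total is 30 patients (same section). The design targets are: "With a threshold value of 45% and expected value of 70% for ORR, one-sided significance level of 5%, and statistical power of 80"%.

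**Assumptions, not in the article.** Scores run from 0 to 100. A single item takes the values 0, 33.3, 66.7 or 100. The share of patients scoring 0 at baseline on a given scale, q, is unknown and is varied from 5% to 50%.

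**The plan's own figure.** No figure is stated for the patient-reported outcomes, so the only one to reproduce is the total of 30. With an exact one-sided binomial test of 45% against 70% at the 5% level, the smallest size with at least 80% power is 25 (16 or more responses, actual level 0.0440, power 0.811). At 30 the rule is 19 or more responses (level 0.0334, power 0.841). The figure of 30 is therefore consistent with the stated design plus an allowance for ineligible patients. The questionnaires play no part in it.

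**Step 1: definition.** Percent change = 100 × (follow-up − baseline) / baseline. Absolute change = follow-up − baseline.

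**Step 2: zero baseline.** From 0 to 33.3, 66.7 or 100, the absolute change is +33.3, +66.7 or +100 points. The percent change is a division by zero in each case, so a newly arising symptom has no value.

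**Step 3: dependence on the starting score.** The same rise of 10 points gives:

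| Baseline | Percent change |
|---|---|
| 0 | undefined |
| 10 | 100% |
| 20 | 50% |
| 40 | 25% |
| 80 | 12.5% |
| 90 | 11.1% |

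**Step 4: asymmetry.** From 33.3 to 66.7: 100 × 33.3 / 33.3 = +100%. From 66.7 to 33.3: 100 × (−33.3) / 66.7 = −50%. The mean of the two is (100 − 50) / 2 = +25%, while the mean absolute change is (33.3 − 33.3) / 2 = 0. A fall can never go beyond −100%, whereas a rise from 33.3 to 100 is already +200%.

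**Step 5: patients without a value.** The expected number is 30 × q. The chance of at least one is 1 − (1 − q)^30.

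| q | Expected number of 30 | Chance of at least one |
|---|---|---|
| 5% | 1.5 | 79% |
| 10% | 3 | 96% |
| 20% | 6 | above 99% |
| 30% | 9 | above 99% |
| 50% | 15 | above 99% |

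These counts take all 30 patients as contributing a baseline questionnaire. They fall in proportion if fewer do.

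**The case against.** The sentence is brief and comes from a condensed article. It does not say that the change is computed per patient, that a mean is taken, or that patients at zero are left out. If percent change were taken on group mean scores, the pair in Step 4 would have a baseline mean of (33.3 + 66.7) / 2 = 50 and a follow-up mean of 50, a change of 0%, and individual zeros would do no harm. A median would dampen extreme values. The phrase may also be loose wording for change in score, and an analysis plan that is not shown could add a rule for zeros. No test, interval or decision rule is attached to these outcomes, and absolute change can always be computed later from the same questionnaires.

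Much of this stands as a limit on the size of the point. It does not remove it: the stated metric is percent change, the per-patient sense is the natural one, and if something else is meant the sentence still needs correcting.

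A reader might go further and infer three things that the article does not support:

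- **That zero baselines will be common and a large part of the data lost.** The article gives no baseline score distribution and no expected mix of performance status within 2 to 4, so only a range can be shown.
- **That benefit will be overstated.** On a symptom scale, leaving out patients who can only worsen flatters the result, but the asymmetry in Step 4 pushes the mean upwards, which there reads as worsening. On a functional scale, leaving out patients who can only improve understates benefit, while the asymmetry reads as improvement. The mechanisms oppose each other.
- **That a mixed model is needed.** The defect lies in the metric, and descriptive means in points already cure it.

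**Conclusion.** The point holds as a badly chosen metric for a descriptive secondary endpoint. Given 0 to 100 scoring and a per-patient calculation, percent change is undefined for every patient at 0 on a scale. For the others it mixes the change with the starting score, strongly at low baselines and mildly at high ones. Across the assumed 5% to 50% range, between 1.5 and 15 of 30 patients per scale would be expected to have no value. The true share, and the net direction of any bias on a given scale, cannot be derived from the article.

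The primary response-rate analysis, its significance level, power and the sample size are untouched. The correction should be made, but the trial's main conclusion does not depend on it.

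**What to change.** Replace the sentence in the Statistical analysis section with one stating that absolute change from baseline in score points will be summarised for each QLQ-C30 and LC13 scale at each scheduled visit, with the number of patients contributing at that visit. Every patient with a baseline and a follow-up score then has a defined value: 0 to 33.3 counts as +33.3 points. If percent change is kept at all, it should be supplementary, with a stated rule for zero baselines.

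A repeated-measures model is optional. With about 30 patients, many visits and dropout that includes death, it brings assumptions of its own.

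The cost is one sentence and negligible extra analysis work. No additional data are needed and the sample size does not change.
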